### Quality control

The trial protocol is developed after consulting experts of acupuncture and moxibustion, orthopedics, statistics, and methodology. All staff will be required to receive training on the trial protocol, participant selection, moxibustion intervention, effect assessment, the usage of the central randomization and data management systems, and the methods to fill out the materials of the trial (e.g. the case report forms), before participating in the trial. Data management will be performed by the Institute of Basic Research in Clinical Medicine, CACMS. Double data entry and strict data audit will be applied. Personal information about patients will be coded using patient identification numbers. Data in the eCRF will be completely anonymized. A three-level quality control system, including self-inspection done by each center, inspection on all centers done by the leading unit, and spot-check auditing done by an independent third party (at the beginning and interim of the study), will be used to further guarantee the quality of the study. To improve patient compliance, research assistants regularly remind participants to receive treatment or assessment via telephone or WeChat. For participants who discontinue or deviate from intervention protocols, we will record the causes and clinical outcomes as much as possible.

## Discussion

The objective of this study is to validate the effectiveness of moxibustion for KOA, and to determine whether the habitat of moxa floss contributes to the effect of moxibustion.

In this trial, we chose KOA as the study disease because it is among those for which the effectiveness of moxibustion has been extensively tested. Also, the alleviation of pain – a key outcome measure for KOA – takes a shorter trial period than other outcome measures to reflect treatment effects. To better observe the between-group differences, we will only enroll participants with moderate to severe KOA.

A three-armed, randomized, controlled trial design including two types of comparison is applied in this trial. The comparison between real and sham moxibustion is to validate the effectiveness of moxibustion for KOA patients; the comparison between two habitats of moxa-stick moxibustion is to demonstrate the correlation between the moxa habitat and the moxibustion effect. For the moxa habitat comparison, we have chosen the TCM-acknowledged optimal habitat (Qichun County, Hubei Province, China) and another large habitat for commercially available moxa products, but which is not recognized by TCM theory (Nanyang County, Henan Province, China). By comparing these two habitats, we aim to make clear whether the habitat of moxa contributes to the effect of moxibustion or not.

The commonly used method for sham or placebo moxibustion is heat-insulated moxibustion using the same moxa material as the real moxibustion [25, 26]. This kind of sham control helps to show the contribution of heat, not the material, to moxibustion. In this trial, we will focus on the part that the material plays in moxibustion. The non-moxa stick, which is made from the leaves of the Artemisia capillaris Thunb, a Chinese herb that belongs to the same family and genus with Artemisia argyi (Artemisia L., Compositae), and shares the same appearance and process with the moxa stick, will be used for sham control. A good patient-blinding effect was achieved in the pre-study assessment. Though it is hard to distinguish two habitat moxa stick moxibustion, the blinding of the practitioner was negatively affected due to a less fragrant odor, looser ashes, and more smoke of the sham moxibustion. However, the failure of practitioner blinding cannot significantly affect the results of this trial, since the independent staff will be responsible for the assessment of the treatment effect. Also, this is a new attempt to provide a kind of blinding method for moxa stick moxibustion.

There are limitations in this study. The sample size lacks strong support for the difference between moxibustion using different habitat moxa floss. The trial duration is short (a 2-week treatment and a 4-week follow-up), since we focus on the short-term analgesic effect of moxibustion. We will not measure the change in the knee joint effusion volume, an objective outcome for KOA, due to the short treatment period. The blindness of the practitioner partly failed in the pre-study assessment, which may bring bias.

In conclusion, results of this trial will show the effect differences of moxibustion between real and sham moxibustion and between moxibustion using different habitat moxa floss, and thus to answer whether moxa floss is a better moxibustion material, and whether the habitat of moxa contributes to the effect of moxibustion. This study will contribute to the research of moxibustion worldwide via publishing results in a peer-reviewed journal (Additional file 1).

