Moxibustion is a traditional Chinese medicine (TCM) therapy involving ignited material to apply heat to certain acupuncture points or areas of the body surface for curing disease through the regulation of the function of meridians and visceral organs [13]. Among the various materials used for moxibustion, moxa floss, a cotton-like material made from dried leaves of Artemisia argyi (a plant commonly known as moxa or mugwort) [13], has survived the test of long-term medical practice and become the most recognized version. Since mugwort is widespread throughout China, there are many habitats for commercially available moxa floss, among which Qichun County, Hubei Province, and Nanyang County, Henan Province become the two largest producers. According to the classical TCM theory, the habitat of moxa floss is crucial to the effect of moxibustion, and the best habitat is granted to Qichun County, Hubei Province. It has been reported that dried leaves of Artemisia argyi native to Qichun County, Hubei Province, produce a higher content of volatile components and a larger output of combustion heat release than those native to other habitats in China [14, 15]. However, this does not imply a similar clinical effect of moxibustion. Though moxa floss native to Qichun County, Hubei Province has been long believed to be the optimal moxibustion material by TCM practitioners, so far there are no clinical studies comparing the moxibustion effect among moxa floss from different habitats. The primary objective of this randomized controlled trial is to compare the effects of moxibustion using moxa floss from Qichun County, Hubei Province (Qichun moxa floss) versus those from Nanyang County, Henan Province (Nanyang moxa floss) in alleviating knee pain for patients with KOA, thus to determine whether the habitat of moxa floss contributes to the effect of moxibustion. The results of this study will also help to validate the effectiveness of moxibustion for KOA via the comparison between moxibustion and sham moxibustion.

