### Statistical methods

#### Sample size

There are no previous clinical studies comparing different habitats of moxa floss, or are there studies comparing moxa floss with non-moxa floss for the effect of moxibustion. Based on the results of a study investigating moxibustion versus a heat-insulated placebo moxibustion for KOA [22], we assumed a standard deviation of 10 for group C (sham moxibustion), and 12 for groups A and B (moxibustion). The sample size calculation was based on the formula of one-way analysis of variance (ANOVA) with pairwise comparisons, with 80% power, a two-sided significance level of 5% and a 15% dropout rate. We designed this study to detect: (1) a difference of 5 points in the WOMAC pain score for comparison between moxibustion using different habitat moxa floss; that is groups A and B with an allocation ratio of 1:1; and (2) a minimal clinically important difference of 10 points [23, 24] for comparison between moxibustion (group A or B) and sham moxibustion (group C) with an allocation ratio of 2:1. For the first comparison, 140 participants will be needed for groups A and B; for the second comparison, 45 participants will be needed for group C, and 90 for groups A or B. The larger result from the first comparison was then used to determine the final sample size, that is, 140 participants in groups A and B, respectively, and 70 in group C. The total sample size is 350 participants.

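### The primary question allows the answer that habitat does not matter, but only gated difference tests are planned, and non-significance cannot support that answer

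*Protocol article*

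**What the plan says.** **Aim.** The Background section of the protocol article makes the comparison of group A (Qichun floss) with group B (Nanyang floss) on knee pain the primary objective, "thus to determine whether the habitat of moxa floss contributes to the effect of moxibustion". The Discussion words the same aim with an explicit negative alternative: "we aim to make clear whether the habitat of moxa contributes to the effect of moxibustion or not". It also describes this comparison in difference terms, as one "to demonstrate the correlation between the moxa habitat and the moxibustion effect". The closing paragraph of the Discussion again says the results will answer the habitat question.

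**Design.** The Sample size section uses the "formula of one-way analysis of variance (ANOVA) with pairwise comparisons", "with 80% power, a two-sided significance level of 5% and a 15% dropout rate". It aims to detect "a difference of 5 points in the WOMAC pain score for comparison between moxibustion using different habitat moxa floss". The only value it calls clinically important is "a minimal clinically important difference of 10 points", given for moxibustion against sham. The assumed SD is 12 in groups A and B and 10 in group C. The result is 140 participants in each of A and B.

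**Analysis.** The Statistical analysis section gives two routes for the primary outcome. One is ANCOVA on the week-2 change with Tukey–Kramer pairwise tests; the other is Kruskal–Wallis with Mann–Whitney tests at P < 0.017. In both, pairwise comparison follows only if the three-group test is significant. No margin is given, and no rule for a null A–B result. The limitations paragraph concedes that the sample size is weakly supported for this comparison.

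**The concern.** A difference test can support a conclusion that the two flosses differ. If it is not significant, the data may show that any difference is small, or they may simply be too imprecise to tell. Only the estimate and its interval separate these cases, and the plan does not tie the conclusion to them.

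The omnibus gate adds to this. If the three-group test is not significant, the plan as written makes no A–B comparison, although A–B is the primary question. On the rank route, a Mann–Whitney P value gives no interval in points to set against the 5 points of the sample size section.

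At stake is how the primary objective may be concluded. Both flosses come from the same species, so little or no difference is a realistic outcome, and for that outcome the plan provides no valid conclusion.

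**Working it through.** **Inputs.** From the Sample size section: difference 5 points, SD 12 in A and B, 80% power, two-sided 5%, dropout 15%, 140 per arm. Completers per arm: 140 × 0.85 = 119.

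**1. Reproducing 140.** The per-arm size for two means is n = 2 × [12 × (z₁₋α/₂ + z₀.₈₀) / 5]².
- With α = 0.05/3 (three pairwise comparisons): 2 × [12 × (2.394 + 0.842)/5]² gives 121. Then 121 × 1.15 gives 140 after rounding up, an exact match; 121/0.85 gives 143.
- With α = 0.05 unadjusted: 91, then 91/0.85 gives 108, which does not match.

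So 140 is the size for a multiplicity-adjusted test of difference.

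**2. Precision at 119 per arm.** SE = 12 × √(2/119) = 1.556.
- Tukey critical value for three groups: 2.356. Half-width 2.356 × 1.556 = 3.66.
- Unadjusted 95%: half-width 1.96 × 1.556 = 3.05.

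**3. What a non-significant result leaves open.**
- A–B is Tukey-non-significant whenever the observed difference is below 3.66.
- The unadjusted 95% interval excludes 5 only if the observed difference is below 5 − 3.05 = 1.95.
- The Tukey interval excludes 5 only below 5 − 3.66 = 1.34.
- At the edge of non-significance, the unadjusted upper limit is 3.66 + 3.05 = 6.71.

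Observed differences from 1.95 (or 1.34) up to 3.66 are therefore non-significant and still compatible with the design difference.

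**4. How often this happens.**
- True difference 5: P(non-significant) = Φ(2.356 − 5/1.556) = Φ(−0.858) = 19.5%, apart from a negligible opposite tail. The omnibus gate can only raise this.
- True difference 0: 98.2% of trials are Tukey-non-significant. The 95% interval excludes ±5 in 79.0% and the Tukey interval in 60.9%. So 98.2 − 79.0 = 19% (37% with the Tukey interval) are non-significant without excluding 5.

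**5. If ±5 were adopted as the margin** (an assumption; the plan sets none). With true difference 0, the chance of concluding no relevant difference is 2Φ(5/1.556 − c) − 1.

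| Interval | c | Chance |
|---|---|---|
| 90% | 1.645 | 88% |
| 95%, unadjusted | 1.960 | 79% |
| Tukey 95% | 2.356 | 61% |

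**6. Sensitivity to the SD.** All of this rests on SD 12, while the Outcome measures section scores pain from 0 to 500 mm, so that 5 points is 5/500 = 1% of the range. With SD 20 (an assumption), the half-widths are 5.08 (95%) and 6.11 (Tukey). Both exceed 5, so no null result could exclude it.

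**The case against.** The strongest reply is that the article announces no equivalence claim. Posing a question with a yes and a no is ordinary wording for a two-sided comparison. The Discussion also states the purpose as demonstrating an association, the sample size is for detecting a difference, and 140 per arm reproduces on that basis. The analysis section attaches consequences only to significant results. The analysis plan, which is not shown, may settle how a null result is reported, and the limitations already express doubt about the A–B sample size.

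Much of this stands:
- A reader might infer that P > 0.05 will be reported as no habitat effect. No section says so.
- A reader might infer that a null result would never exclude 5 points. It often would: in 61% to 79% of trials with no true difference, on the planning inputs.
- A reader might take 5 points as the equivalence margin. It is the difference to detect. The largest difference compatible with any Tukey-non-significant result is 2 × 3.66 ≈ 7.33, below the 10 points called clinically important for the sham comparison, so what counts as excluded depends on the margin chosen.
- A reader might infer that the design itself is wrong. A difference test sized for 5 points is a legitimate design for finding a habitat difference.

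What does not fall away is the mismatch within the article itself. The Background and Discussion promise an answer that may be negative, while the stated test sequence can yield only a positive one and may omit the A–B comparison altogether. Leaving reporting detail to an analysis plan does not remove a gate that the article states.

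**Conclusion.** The point holds in a limited form. As written, a non-significant result could not support the conclusion that habitat does not contribute: it covers observed differences up to 3.66 points, whereas 5 points is excluded only below 1.95 (95% interval) or 1.34 (Tukey interval). A true 5-point difference would be missed in about 20% of trials. These figures assume SD 12, 15% dropout and normal-theory intervals, with no allowance for any precision gained by baseline adjustment.

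Nor do the documents support a claim that the trial clearly has enough precision for a negative answer. The chance of one at ±5 ranges from 61% to 88% with the interval chosen, and it disappears if the SD on the 0–500 mm scale is well above 12. This is an inexpensive improvement to how the primary question is answered and does not call for a redesign.

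**What to change.** 1. Report the ANCOVA-adjusted A–B difference with its two-sided confidence interval whatever the omnibus result, and also if the rank tests are used for significance.
2. State that a non-significant A–B result is inconclusive unless that interval excludes a pre-specified margin. Fix the margin and the interval (90%, 95% or Tukey) before unblinding, on the scale actually used for the WOMAC pain score. The 5-point design difference is a candidate that the sponsor would have to justify.
3. If no margin can be justified, remove the negative half of the aim from the Discussion and present the comparison as a search for a difference.

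Cost: wording in the analysis plan and the article, with no extra participants. The downside is that some null results must be reported as inconclusive. With ±5, SD 12 and no true difference, that would be about 19% of trials with the 95% interval and 37% with the Tukey interval.

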### Trial status

This trial is currently recruiting participants.

## Abbreviations

AEs: Adverse events
ANCOVA: Analysis of covariance
KOA: Knee osteoarthritis
NSAIDs: Nonsteroidal anti-inflammatory drugs
OA: Osteoarthritis
OMERACT-OARSI: Outcome Measures in Rheumatology Arthritis Clinical Trials-Osteoarthritis Research Society International
PGA: Patient global assessment
TCM: Traditional Chinese medicine
VAS: Visual analogue scale
WOMAC: Western Ontario and McMaster Osteoarthritis Index
